## Abstract

**Background:**

Severe knee osteoarthritis, as well as the surgical procedure of total knee replacement that aims to reduce its symptoms, cause great deterioration on the proprioceptive system. Taking this fact into account, and considering that balance abilities positively influence the capacity to perform basic functional tasks, this trial aims to find the short and mid-term effects of a preoperative balance and proprioceptive training when conducted by patients undergoing total knee replacement. Along with the effects, it is intended to determine whether in-home based training can be as effective as hospital training. The results will help to conclude whether the possible benefits may outweigh the health costs.

**Methods:**

Seventy-five participants will take part. The trial will include in-home and supervised hospital experimental training compared to a non-active control group in order to estimate the actual effect of the proposal against the benefits due exclusively to the surgical procedure. Interventions last 4 weeks prior to surgery, and the follow-up will be at 2w, 6w, and 1y following the operation. The primary outcomes are in agreement with the goals: self-reported functionality in terms of KOOS and overall balance in terms of the Berg Balance Scale. The secondary outcomes will include the measurements of static and dynamic balance abilities, pain, function, and quality of life.

**Discussion:**

It is expected for the results of this trial to provide relevant information in order to decide if a specific intervention is cost-effective to be implemented in clinical practice.

**Trial registration:**

Clinicaltrials.gov identifier NCT03100890. Registered in April 4, 2017.

## Background

Total knee arthroplasty is a solution for severe osteoarthritis in advanced stages, when functional disability and especially pain are difficult to alleviate with conservative treatment and drugs. The aging of the population, the high prevalence of the condition, the progress in surgical techniques, the level of satisfaction, along with the increase of the quality of life of the patient, are factors that have made this a common procedure [1, 2].

In spite of the overall satisfactory outcomes, some patients may present pathological gait patterns, difficulty in performing basic functional tasks, and in maintaining balance and postural control, even one year after surgery [3–5]. In order to optimize outcomes, the procedure ought to be accompanied by physiotherapy. Systematically, an early postoperative intervention is recommended [6]. Also, while it is true that the literature is not conclusive regarding mid and long-term effects [7], a preoperative program is always advisable, can optimize early results, and reduce the length of stay [8]. By contrast, it is time consuming and expensive, thus being necessary to conduct cost-effectiveness analyses that justify the use of such program [8–10].

Physiotherapy generally focuses on strengthening exercises and functional performance based trainings. Balance and proprioception work is usually included in training programs, but to a lesser extent. However, the recovery and enhancement of these aspects may be a determining factor, since good balance abilities positively influence the capacity to perform basic functional tasks [11]. Taking this relationship into account, and that both the condition itself and the high invasiveness of the surgical procedure involve a significant deterioration of the proprioceptive system [12], seems interesting to appraise a proposal of intervention which begins in the preoperative phase, and looks for benefits not only among the muscular and functional outcomes, but also in sensorimotor terms.

Balance and proprioceptive approaches have been referred to as sensorimotor and neuromuscular trainings. A recent qualitative review suggested that these may be an acceptable adjunct to usual care in physiotherapy [13]. Nevertheless, the literature is scarce with respect to the impact of an additional training specifically oriented towards the recovery of balance and proprioception. Gstoettner et al. [5] suggested that balance and proprioceptive training is effective in improving standing balance, can avoid pathological gait patterns and falls, and proposed that further investigations were needed in order to give consistency to the findings. Later, Hubber et al. [14] and Villadsen et al. [15] evaluated the effects of a preoperative neuromuscular training program, while Fernandes et al. [16] analyzed the cost-effectiveness of the latter. None of them performed a comparative study between hospital and in-home intervention appraising the effects, pragmatism and costs.

With this background, this trial will determine the short and mid-term effects of a preoperative balance and proprioceptive training when conducted by patients undergoing total knee replacement, and the impact that this may have on the balance of the patient, functionality and quality of life [17]. Along with the effects, it is intended to determine whether in-home based training can be as effective as hospital training. The results will help to conclude whether the possible benefits may outweigh the health costs.

## Method

### Design and ethics

This is a 3-arm randomized trial, which is carried out prospectively at Hospital Universitario y Politécnico La Fe of Valencia, Spain. The trial has been designed in accordance with the guidelines proposed in the Helsinki Declaration, was approved by the Ethical Committee for Clinical Research and by the Scientific Committee of the mentioned hospital, and was prospectively registered in April 4, 2017 (clinicaltrials.gov identifier NCT-03100890).

Potential participants must give express consent for the use of data for exclusively scientific and research purposes. The data are anonymized from the origin, with initials and numerical identifiers for the electronic bases. The data will be extracted by the evaluators and managed exclusively by the principal investigator of this project, who will be the only one with access to the complete database. The database will be kept in the Physiotherapy Department of the University of Valencia, subject to the center’s security protocols.

### Participants

Potential participants are invited to participate by the orthopedic surgeon, who performs an initial check of whether the criteria are met. The criteria will include those subjects over 60 years of age, with severe knee osteoarthritis, who will undergo their first surgery for total arthroplasty, and present a low risk of falling with a score of over 40 on the Berg Balance Scale [18] and a moderate cognitive condition to adequately follow the interventions, with more than 20 points in the Spanish version of Lobo of the Mini-Mental State Examination [19]. In case the surgeon refers the potential participant to the rehabilitation department for possible inclusion, the last 2 criteria are evaluated by the rehabilitators. Criteria exclude those subjects with central or vestibular affections that directly affect their balance, or with postoperative complications as possible infections. If the potential participant meets the criteria, reads and understands the information sheet, and signs a consent form, become a participant in the trial. Those potential participants on a waiting list whose date of surgery is established for less than 20 days are not considered for inclusion. In the case of modifications of the date of surgery, the participant will continue forming part of the study, as long as the date is not modified beyond 30 days. The participants flow chart is shown in Fig. 1.

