### Blinding and randomization

Participation occurs sequentially. At the time that a subject has an established date of operation, the physician checks the criteria are being met. If so, the potential participant is informed of the study and is referred to the rehabilitation department where, if is definitely admitted will take part in the randomization process. The randomization is generated from the output of the Matlab® statistical program by external assessor. A physiotherapist with 3 years of experience and blinded to the intervention groups will be in charge of the outcome assessment. The blinding of the participants is not assured, as they are informed about the trial before randomization. Neither is it the blinding of those who provide the treatments for the same reason. However, physiotherapists do not take part in the process of randomization and participant allocation. The external assessor in charge of the randomization is blinded to the intervention groups that have a numerical coding, and will receive the data of the participants for the statistical processing. The interpretation of the results will be carried out by the whole team.

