#### Dealing with missing data

Every effort will be made to reduce sample loss, particularly with regard to mid-term monitoring (1y). In the event that a participant cannot or decides not to attend the follow-up evaluation, it is proposed to resolve the self-reported surveys at home and forward them via email, or the possibility of the evaluator’s displacement is also granted. To deal with missing data, we will compare the baseline characteristics of those patients who have and have not been evaluated in search of potential sources bias in the results of the complete analyses. It is also intended to obtain a record of the reasons for drop-out and then evaluate the best mechanism of data analysis, with methods to impute data and reanalyze it with the intention to treat, and thus evaluate the possible impact on the conclusions [31].

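### As written, two eligibility rules take patients out after randomisation, one on an event the training could influence, and intention-to-treat appears only as a re-analysis

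*Protocol article*

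**What the plan says.** All references are to the protocol article.

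- **Participants, exclusions:** "Criteria exclude those subjects with central or vestibular affections that directly affect their balance, or with postoperative complications as possible infections".
- **Participants, inclusion:** patients "who will undergo their first surgery for total arthroplasty".
- **Participants, moved surgery dates:** "the participant will continue forming part of the study, as long as the date is not modified beyond 30 days".
- **Blinding and randomization:** the patient goes to the rehabilitation department and "if is definitely admitted will take part in the randomization process". Table 2 places randomisation in the enrolment column, ahead of the baseline assessment.
- **Abstract, Methods:** "Interventions last 4 weeks prior to surgery".
- **Blinding and randomization, on masking:** "The blinding of the participants is not assured, as they are informed about the trial before randomization". The treating therapists are not masked either.
- **Dealing with missing data:** evaluated and non-evaluated patients are compared at baseline to look for bias in the complete analyses. Drop-out reasons are recorded, and the team will then "evaluate the best mechanism of data analysis, with methods to impute data and reanalyze it with the intention to treat", to judge the effect on the conclusions.
- **Data analysis:** the main comparison is a repeated-measures ANOVA, or an ANCOVA if baselines differ. No analysis population is named.

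**The concern.** An exclusion criterion should be decidable before allocation. A complication of an operation that has not yet happened is not. Here it becomes known only after the patient has been randomised and has gone through the preoperative period in which two of the three arms train. Preoperative exercise could plausibly change who has a complicated recovery. Removing such patients would then select on a consequence of treatment, and an arm with more complications would look better because its worst patients had left.

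The 30-day rule also applies to people who are already participants. It is a weaker worry, because nothing in the document suggests that allocation moves a surgery date.

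The missing-data text offers no firm safeguard. Intention-to-treat comes as a second look, by a method settled after the reasons for loss have been seen. At stake are the postoperative contrasts at 2 weeks, 6 weeks and 12 months, including the two times that the Data analysis section singles out. If removed patients are never assessed, their outcomes cannot be recovered later.

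**Working it through.** **1. Order of events.** Eligibility and consent, then randomisation (Table 2, enrolment), then baseline assessment, 4 weeks of training in two arms, surgery, and visits at 2 weeks, 6 weeks and 12 months. A postoperative complication of the trial operation can occur only after surgery. A change of surgery date can occur at any time after enrolment. On this reading both rules can act after randomisation, and the complication rule acts after the randomised treatment.

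**2. The plan's own figures.** Inputs from Sample size: group means 53, 53 and 48 on the Berg scale, SD 4.5, α = 0.05.

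- The SD of the three means is √[((5/3)² + (5/3)² + (10/3)²)/3] = 2.357, so f = 2.357/4.5 = 0.524.
- The noncentral F with 20 per group gives power 0.952. The article states no power. Its 20 per group is the smallest size that reaches 95%.
- Allowance for 20% loss: 60/(1 − 0.20) = 75, or 25 per arm. This reproduces the stated total.

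**3. Possible bias.** The document gives no complication rate, so everything in this step is an assumption. Suppose training has no true effect. A share q1 of one arm and q0 of another are excluded, and excluded patients average D Berg points below those retained. Each retained mean then exceeds its full-arm mean by q × D, so the between-arm bias is (q1 − q0) × D, in favour of the arm that loses more patients. With SE = 4.5 × √(2/20) = 1.423 at 20 per arm, the two-sided type I error (normal approximation) is:

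| Rates | D | Bias (Berg points) | Share of planned 5 | Type I error |
|---|---|---|---|---|
| equal | any | 0 | 0% | 0.050 |
| 5% vs 10% | 4.5 | 0.05 × 4.5 = 0.225 | 4.5% | 0.053 |
| 5% vs 10% | 9 | 0.05 × 9 = 0.45 | 9% | 0.062 |
| 4% vs 12% | 4.5 | 0.08 × 4.5 = 0.36 | 7.2% | 0.057 |
| 4% vs 12% | 9 | 0.08 × 9 = 0.72 | 14.4% | 0.080 |

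With 25 per arm, 4% versus 12% is one patient against three. The values of D are one and two planned SDs. The zero in the first row requires equal severity as well as equal rates.

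**4. Can the trial afford to keep everyone?** ANOVA power under the plan's assumptions, if retaining these patients dilutes the assumed effect (the dilution is an assumption):

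| Effect retained | f | Power, 25 per arm | Power, 20 per arm |
|---|---|---|---|
| 5.0 points | 0.524 | 0.984 | 0.952 |
| 4.5 points (10% lost) | 0.471 | 0.956 | 0.900 |
| 4.0 points (20% lost) | 0.419 | 0.899 | 0.815 |

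The planned 75 can carry an intention-to-treat primary analysis.

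**The case against.** Several points can fairly be made for the plan.

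- **Removal of data is inferred.** Nothing says that collected data are deleted or that visits stop, and the participant flow chart is not available here. The Discussion says that the exclusions serve safety in delivering the interventions, which also fits stopping exercise without stopping follow-up. This stands as a limit on certainty. But nothing says that such patients are still followed and analysed as allocated, and the 30-day sentence is about remaining in the study, not about remaining in the exercise programme.
- **The criterion might mean earlier surgery.** A first arthroplasty does not rule out a previous operation of another kind, and the criterion sits in the entry list. That reading is possible, but it is the less natural one.
- **A reader might infer that the complete-data analysis is declared primary.** It is not. The missing-data text implies an order but ranks nothing, and a condensed article may leave the analysis set to a fuller document. What stands is the stated sequence: reasons for loss first, choice of method next, intention-to-treat as a re-analysis.
- **A reader might infer that complications would go unreported.** The document does not support this. Data analysis plans an evaluation of adverse effects at 6 weeks, drop-out ratios and survival analyses, and the reasons for drop-out are to be recorded.
- **A reader might treat the 30-day rule as a second source of bias between arms.** No mechanism is shown. Loss unrelated to arm mainly costs numbers, for which the sample size makes an allowance.

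**Conclusion.** The point holds. Followed as written, the Participants section removes patients on events that arise after randomisation, and one of those events could be affected by the treatment under test. The missing-data section does not commit in advance to analysing everyone as randomised.

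The fault lies in how the compared population is defined. It is not a demonstrated large bias. Under the assumed differential rates the shift is about 0.2 to 0.7 Berg points against the planned 5, with type I error of 0.053 to 0.080. It is nil when rates and severity are the same in every arm. Larger shifts can be produced by placing every complication in one arm with a very large deficit, but the document gives no basis for that scenario. Nor does it support the flat statement that the arms compared will no longer be the randomised arms. That depends on how many patients are removed and whether they are still assessed, and the text leaves both open.

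The conclusion rests on reading the complications as those of the trial operation, and the 30-day sentence as ending participation.

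**What to change.** - Separate treatment from follow-up. Leave any safety decision about continuing the exercise programme to clinical care. State in Participants that a postoperative complication or a postponed operation neither ends follow-up nor removes a patient from the analysis. The safety-based criterion need not be deleted for this purpose.
- Define the primary analysis as all randomised patients in their allocated arm, using all available visits. Use a mixed model, or multiple imputation specified before outcome data and drop-out reasons are examined.
- Report complications and postponements by arm.
- Keep the set without complications or long postponements as a labelled sensitivity analysis.

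The cost is some protocol wording, a few extra follow-up visits and slightly more outcome variance. The power figures above show that the planned 75 can absorb this under the plan's own assumptions.

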#### In-hospital supervised preoperative intervention (PRE_ EXP1)

Different exercises are proposed and developed over the course of the 12 sessions on alternate days, divided in 4 weeks of training. On the one hand the intervention includes a standard program of rehabilitation with strengthening exercises. In addition, each session includes a total of 4 to 5 balance and proprioceptive exercises performed over a period of 20 min. The training has been based on the Fitzgerald principles to train proprioception, on previous of our works, and on clinical experience [21, 23]. The first 2 weeks are oriented to enhance balance and proprioception with the side, treadmill, cross, and tandem walk exercises. These exercises are excluded in weeks 2 and 3 and multiple changes of direction, foam activities and balance work with the Bohler plate are performed instead. Also 5 min training of weight bearing and testing the limits of stability are performed during the last 4 sessions. Progression in the exercises is implemented as tolerated, always trying to avoid fatigue. The physiotherapist is responsible for recording attendance at rehabilitation sessions.

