#### In-home preoperative intervention (PRE_EXP2)

The in-home exercise program is essentially based on the same principles than PRE_EXP1, but adapted so it can be conducted at home. The first day is an education with the explanation of the exercises. The training is carried out in the hospital and is supervised by the physiotherapist. The participant is asked to repeat the exercises, and possible doubts are resolved. The intervention consists of a phase with exercises to strengthen the main musculature of the lower limb, and a second phase of balance and proprioceptive work. The muscular enhancement exercises are isometric quadriceps in extension, elevations of the lower limb with knee in extension, ankle in dorsal flexion, and slight hip flexion combined with abduction and adduction. Additionally, the middle gluteal and open chain quadriceps are also performed. Each set of exercises is performed in 4 series consisting of 10 repetitions with a rest of 90 s between each series. The proprioception exercises consisted of tandem position and walking, single-leg position, and treadmill walking. Each exercise has to be performed for 2–4 min. And the participants were asked to do so safely, for instance in a hallway or in front of a table or chair, to avoid falls. After session 6, the participant is appointed for a reminder and verification of exercises, as well as possible corrections in the implementation of the intervention. The participant is requested to register the number of sessions performed in a calendar. The physiotherapist phones the participants on a weekly basis, in order to check both the compliance of the program and the calendar fulfillment.

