#### Outcome assessment

The baseline assessments will be carried out by a physiotherapist blinded to the interventions, following the signing of an informed consent form and prior to the start of the physiotherapy sessions. The proposed time for the outcome evaluation is in the preoperative period (baseline, between 8 and 4 weeks), before (1 week) and after (2 weeks) the surgical procedure, after the postoperative intervention (6 weeks) and 12 months follow-ups. Details are given in Table 2.

**Table 2 Tab2:** Detail of variables and times for evaluation of outcomes

Time point	Enrolment	BL	BP	AP	AI	12 m
Eligibility screen	x					
Informed consent	x					
Randomization	x					
Assessments						
Demographic and biomedical	x					
Primary						
Self-reported functionality	KOOS	x	x	x	x	x
Balance (overall)	Berg Balance Scale	x	x	x	x	x
Secondary						
Function	ROM (flexion)	x	x	x	x	x
	ROM (extension)	x	x	x	x	x
	Strength	x	x	x	x	x
Balance (dynamic)	Timed Up & Go	x	x	x	x	x
(static)	One-leg Stand	x	x		x	x
(stability)	Functional Reach	x	x	x	x	x
Quality of Life	EuroQoL	x			x	x
Anxiety	EuroQoL(5D)	x	x		x	
Cost-effectiveness						
	Qaly					x
Patient expectations						
		x			x	x
Interventions		BL	BP	AP	AI	12 m
Non-active comparator				x------x		
In-hospital preoperative		x------x		x------x		
In-home preoperative		x------x		x------x		

*BL* Baseline, *BP* Before procedure, *AP* After procedure, *AI* After intervention, *KOOS* Knee Injury Osteoartritis Outcome Score, *ROM* Range of Movement in degrees, *Qaly* Quality adjusted life year

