The design of the interventions has been realistic, and the information provided by clinicians with long experience and by the patient feedback has been fundamental. The experimental intervention at home (PRE_EXP2) has been designed to cover the basic aspects of the one performed in the hospital (PRE_EXP1). Certainly the possibilities of supervised work and hospital instrumentation are not available at home, but this has been taken into account and the adaptation of the intervention was made considering a pragmatic design.

Inclusion criteria are broad, not restricted to a large number of patients with comorbidities, which will increase the applicability of the proposal. The exclusion criteria have been proposed not to promote the results, but only for reasons of safety in the implementation of interventions. Therefore there is no exclusion due to social disadvantages, depression, anxiety or poor motivation, which are often frequent.

The trial began the recruitment of participants in March 2017. We expect to finalize the recruitment by June 2018. Early-postoperative outcome data are expected to be available from October 2018. Follow-up evaluations will be performed during 2019. The trial is expected to be completed by the end of 2019.

This work will serve as a basis for reducing implementation bias. In case of substantial changes in the protocol, they will be duly reported with the reasons.

It is necessary to recognize limitations such as the fact that the follow-up is prolonged beyond usual in clinical practice, and that some of the measures are not always used by clinicians, although they are indeed used in research. We plan to share, critically appraise and disseminate the results by offering critical discussion of the findings, description of potential clinical impact, clinical application, and contextualization within contemporary literature.

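### The 20-day minimum lead time to surgery contradicts the 4-week, 12-session preoperative programme and the baseline window of 8 to 4 weeks

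*Protocol article*

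**What the plan says.** Four statements in the protocol article bear on the preoperative calendar.

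- **Eligibility (Participants):** "Those potential participants on a waiting list whose date of surgery is established for less than 20 days are not considered for inclusion". A patient exactly 20 days from surgery is therefore eligible.
- **Length of training (Abstract, Methods):** "Interventions last 4 weeks prior to surgery".
- **Dose in the hospital arm (In-hospital supervised preoperative intervention):** exercises are "developed over the course of the 12 sessions on alternate days, divided in 4 weeks of training". The home arm has no session total of its own, but "The in-home exercise program is essentially based on the same principles than PRE_EXP1".
- **Assessments (Outcome assessment):** "The proposed time for the outcome evaluation is in the preoperative period (baseline, between 8 and 4 weeks), before (1 week"; the sentence then lists the postoperative visits. The same section places baseline after consent and ahead of the first session.

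The Participants section also deals with surgery dates that move after entry: "the participant will continue forming part of the study, as long as the date is not modified beyond 30 days". That rule covers a changed date, not a short lead time at entry.

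**The concern.** The eligibility floor is 8 days shorter than both the training course and the late edge of the baseline window. A site that follows the eligibility sentence exactly will enrol patients who cannot follow the visit and treatment schedule. The article gives no shortened programme and no second baseline window for them.

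What is at stake is the delivered dose. Participants with a short lead time would be analysed as having received a 4-week programme that they could not complete, which blurs what was tested. In all three arms, including the control arm, their baseline would also be measured later than proposed. Attendance records in the hospital arm and calendars in the home arm would show the shortfall but would not prevent it.

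**Working it through.** **Inputs.** Minimum lead time 20 days (Participants). Course of 4 weeks = 28 days (Abstract, Methods). Twelve sessions on alternate days in 4 weeks (In-hospital intervention). Baseline no later than 4 weeks, and the pre-surgery assessment (BP) 1 week, before surgery (Outcome assessment).

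**The plan's own dose.** 4 weeks × 3 sessions per week = 12 sessions, so the stated dose and length agree with each other. The conflict is with the eligibility floor.

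**Baseline window.** The late edge is day 28 before surgery. At a lead time of L days, baseline is 28 − L days late: 28 − 20 = 8 days at the floor and 28 − 27 = 1 day at L = 27. This holds in every arm.

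**Sessions that fit.** Assumptions: the first session is on day 0, surgery is on day L, and training continues up to the day before surgery. The article does not fix the exact weekly pattern, so two are counted.

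- Strict alternate days: sessions on days 0, 2, …, 22.
- Three per week (Monday, Wednesday, Friday): for a Monday start, days 0, 2, 4, 7, 9, 11, 14, 16, 18, 21, 23, 25. For a Wednesday or Friday start, the last session is on day 26.

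| Days to surgery | Alternate days | Three per week (over the three start days) |
|---|---|---|
| 20 | 10 | 9 |
| 21 | 11 | 9 |
| 22 | 11 | 10 |
| 23 | 12 | 10 |
| 24 | 12 | 10–11 |
| 25 | 12 | 11 |
| 26 | 12 | 11–12 |
| 27 | 12 | 12 |
| 28 | 12 | 12 |

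At three per week the day-20 count can fall to 8 if the first available day is not a training day.

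**If training stops at the 1-week assessment.** 20 − 7 = 13 usable days. Seven sessions fit on alternate days (days 0 to 12), and 5 to 6 at three per week.

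**Content of the sessions lost.** In the hospital arm, 5 minutes of "training of weight bearing and testing the limits of stability are performed during the last 4 sessions", that is, sessions 9 to 12. With the programme delivered in order and training up to surgery, a day-20 patient reaches 10 − 8 = 2 or 9 − 8 = 1 of these four.

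**Does a 28-day floor suffice?** The 12th session falls on day 22 (alternate days) or day 25 to 26 (three per week). That leaves 28 − 22 = 6 days, or 28 − 26 = 2 to 28 − 25 = 3 days, for the pre-surgery assessment, if training starts on the baseline day. If that assessment stays a full week before surgery and training must end by then, 28 − 7 = 21 days remain: 11 sessions on alternate days or 9 at three per week. The full 4 weeks would then need 28 + 7 = 35 days.

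**The case against.** The strongest reply is that this is a pragmatic trial on a surgical waiting list, where dates move and some incomplete delivery is expected. Lead time is fixed before randomisation, so the arms are affected alike. The baseline window is described as proposed. On the article's literal alternate-day spacing, only patients at 20 to 22 days lose sessions, and then only 1 or 2 of 12. These points stand and limit the consequences. They do not remove the contradiction: at 20 to 27 days neither 4 weeks of training nor a baseline inside the window is possible.

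A reader might infer three stronger things that the document does not support.

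- **That the balance training itself is lost.** The hospital programme has 20 minutes of balance and proprioceptive exercises in every session. The block reserved for the last four sessions adds 5 minutes. It is described for the hospital arm only, and its loss depends on delivery in order. The exercises listed for the home arm include no such block, and applying 12 sessions at home is itself an assumption.
- **That the comparison is biased.** Nothing shown favours an arm.
- **That a definite amount of power is lost.** The Sample size section states no power, and the article does not say how many patients would enter at 20 to 27 days. A figure would need an invented share and an assumed dose-response.

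**Conclusion.** The eligibility floor is wrong as written. It admits patients at 20 to 27 days who must miss the baseline window by 1 to 8 days in every arm and who, if allocated to training, cannot have the 4-week course.

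The loss of sessions is smaller and conditional. With training up to surgery, a day-20 patient can fit at most 10 of 12 on strict alternate days or about 9 at three per week, and 5 to 7 if training ends at the 1-week assessment. On strict alternate days all 12 fit from day 23, so at days 23 to 27 only the 4-week span and the baseline window are missed. These counts rest on an assumed weekly pattern and a first session on the day from which lead time is counted. Screening, consent, randomisation and baseline take time, so real training time may be shorter.

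The effect on the results cannot be sized from the document. Severity is minor to moderate.

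**What to change.** For new patients, change the exclusion to fewer than 28 days between the baseline assessment and the scheduled surgery. Use the same anchor in all three arms and check it before randomisation, from the booked baseline date if that visit is still to come. The first training session should not be the anchor, because the arm is not yet known and controls have no such session.

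Start training promptly after baseline. At three per week the 28 days leave only 2 to 3 days after the final session, and each day of delay uses one of them. Hold the BP assessment in the last week before surgery, after the final session, with the same window in the control arm. If the sponsor prefers to keep it a full week before surgery with training complete, the floor should be about 35 days.

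The article reports that "The trial began the recruitment of participants in March 2017", so some patients may already have entered under the old rule. Keep them in the analysis as allocated, and report sessions delivered by lead time.

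The cost is an amendment to one eligibility sentence and one visit window. Waiting-list patients at 20 to 27 days become ineligible, which may slow recruitment of the 75; their number is not given. A surgery date brought forward after entry can still shorten some courses.
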